## Materials and methods

### Study design

This study will be a case-control study nested into a hospital-based, single-center, observational neonatal cohort. Recruited preterm neonates will be followed over their first 28 days of life. The primary clinical endpoint in this study is a blood culture (BC)-proven LOS. Secondary endpoints are clinical sepsis, NEC, death to clinical and/or BC-proven sepsis or NEC, death to any cause, or discharge from the hospital with or without sequelae.

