### Study population and sample size

The study participants will include inborn and outborn preterm neonates born at 28 + 0 to <34 weeks of GA admitted to the neonatal wards, and their respective mothers who consented to participate after a detailed description of the study has been given by trained study team members. Recruited preterm neonates should have a minimal weight of at least 1000 g and be enrolled within their first week of life. We will exclude infants whose mothers are below 18 years of age, have severe, life-threatening illness at the time of admission, and/or have severe comorbidities or severe congenital malformations. Furthermore, neonates or mothers who ever received probiotic supplements during pregnancy will be excluded from this study.

Sample size calculations considered all study objectives and the one requiring the largest sample size will be the basis to determine recruitment numbers. All eligible preterm neonates admitted to the neonatal unit during the 18-month study period will be recruited and closely followed up for 28 days each.

To answer the primary research question on the hypothesis of preterm neonates developing gut dysbiosis before the onset of sepsis we need to identify preterms with BC-proven sepsis, assess their microbiomes, and compare it with controls (matched for GA, sex, mode of delivery, type of feeding, and previous antibiotic exposure). Assuming a rate of BC-proven sepsis of 10% and 25% missed samples we expect to identify 72–135 bloodstream pathogens (positive BCs) with 54–101 complete sets of stool samples for microbiome analysis within 18 months [7,10]. According to Graspeuntner *et al.,* we then expect gut dysbiosis in 30% of the neonates without and 60% of the children with LOS [19].

Our minimal sample size considerations are based on the proportions of gut dysbiosis in children with and without LOS. Assuming an alpha level of 5% and a power of 80% a minimal study number of 84 children (42 with and 42 without LOS) is needed to reject the null hypothesis that no difference in the proportion of dysbiosis between both cases and controls. Cases are defined as preterm neonates who develop LOS and controls as preterm neonates who do not develop any clinical or culture proven sepsis during the observation period (after 72 hours of life).

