### Variables to predict LOS and gut dysbiosis

Variables have been selected based on a literature search and local clinical experience. Table 1 shows factors predicting LOS and gut dysbiosis that will be captured during the study period. Independent variables will be categorized as socio-economic, neonatal, maternal, and septic risk factors (Table 1).

**Table 1 pone.0325099.t001:** Candidate variables for predicting LOS and gut dysbiosis.

Socio-economic factors	Neonatal factors	Maternal factors	Septic risk factors
Maternal education level	Gestational age	Age at delivery	Invasive ventilation
Self-rated household income	Sex	Parity	Central line at least 48 hrs
Family health insurance	Birth weight	Previous stillbirths	Parenteral nutrition
	Multiple births	HIV status	Presence of any maternal risk factors
	APGAR score at 1 minute	Medical conditions	Type of feeding
	APGAR score at 5 minutes	Pregnancy complications	
	Place of birth	Maternal antibiotic exposure 3 months before delivery	
	Delivery complications		
	Antibiotic exposure and type		
	Type of delivery		

During the observational period of 28 days clinical signs and symptoms of LOS and/or NEC, BC results with phenotypic identification, and antibiotic susceptibility testing, the previous use and type of antibiotics, and the clinical outcomes, will be recorded by the study team in electronic data capture forms. Stool samples for microbiome analysis will be collected in a standardized manner on day 1–3, and days 7, 14, 21 (each ±3) and neonates’ type of feeding in the last 24 hours will be categorized as exclusive human milk (no formula given), breastfed mainly (>80% feeds breastmilk/human milk), formula feed (>50% of feeds include formula), only formula (no human milk), or no enteral feeding at all.

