### Statistical analysis

Descriptive statistics will be used to summarize the demographic and clinical characteristics of the study population, including gestational age, birth weight, gender, mode of delivery, and presence of comorbidities. Mean and standard deviation or median and interquartile range for continuous variables will be used and for categorical data frequencies or proportions will be described.

To answer the first objective on the incidence and risk factors of LOS, the incidence density will be calculated as the number of new cases of LOS divided by the total person-time at risk in the cohort. The person-time at risk will be calculated by summing the individual follow-up durations until the occurrence of BC-proven LOS (clinical sepsis, NEC, and death).

Cox-proportional hazard regression will be utilized to investigate the relationship between the risk factors and risk to develop primary and secondary endpoints. First, we will perform univariate cox-regressions for potential risk factors to identify individual risk factors, all variables considered relevant for the study question will be included in the multivariate cox-regression to adjusting for potential confounders. The hazard ratios (HRs) with the 95% confidence intervals (CIs) will be estimated for each risk factor. Etiological agents of LOS/NEC and the respective AMR patterns will be described as the proportion of isolates resistant to each antibiotic and according to international standard.

Microbiome analysis will be performed to evaluate gut dysbiosis in preterm infants prior to the development of LOS and in relation to the microbiome of the mother. Association of relative abundances of microbial species with the factors of gestational age, days of life, diet, and LOS will be limited to species that were found with a non-zero relative abundance in at least 40 stool metagenomes. Square root-transformed relative abundancies will be used and analysed using linear mixed effect (LME) models, where repeatedly collected microbiome data from each child is considered to cluster.

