Antibiotic interventions following a LOS diagnosis are likely to have a strong impact on the microbiome composition. Statistical analyses will be performed using the latest version of R statistical software. Cox regression will be calculated using the *survival* package and LME using the *lme4* package. In all above-mentioned association tests, samples taken after LOS diagnoses will be excluded from the statistical analysis since the present study focusses on the microbial pattern that precedes LOS.

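### The microbiome mixed model leaves out pre-sample antibiotic exposure and mode of delivery, so the LOS effect can carry residual confounding; the feeding categories also have a gap

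*Protocol article*

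**What the plan says.** Under Study design the article states: "This study will be a case-control study nested into a hospital-based, single-center, observational neonatal cohort". Under Study population and sample size, controls are "matched for GA, sex, mode of delivery, type of feeding, and previous antibiotic exposure".

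The Statistical analysis section gives the species-level model as "Association of relative abundances of microbial species with the factors of gestational age, days of life, diet, and LOS", limited to species present in at least 40 stool metagenomes. It uses an LME on square-root-transformed abundances, "where repeatedly collected microbiome data from each child is considered to cluster". No other fixed factor and no other cluster level is named.

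On antibiotics, the same section says: "Antibiotic interventions following a LOS diagnosis are likely to have a strong impact on the microbiome composition". It then drops samples taken after a LOS diagnosis. The section on variables says "Table 1 shows factors predicting LOS and gut dysbiosis that will be captured during the study period", and the table includes antibiotic exposure and type, type of delivery, and multiple births. It adds that "the previous use and type of antibiotics, and the clinical outcomes, will be recorded by the study team".

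The same section defines the intermediate feeding groups as "breastfed mainly (>80% feeds breastmilk/human milk), formula feed (>50% of feeds include formula", between exclusive human milk and formula only, with a further group for no enteral feeding.

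**The concern.** The primary research question is whether dysbiosis precedes LOS or NEC. Antibiotics given before LOS can alter the stool microbiome, and exposed infants may also differ in LOS risk. The protocol lists antibiotic exposure and delivery type as predictors of both, so both are potential confounders of the LOS term. A model without them relies wholly on the matching. If that is incomplete, part of an antibiotic effect can be reported as dysbiosis before LOS.

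The plan does not treat matching as sufficient elsewhere: gestational age and feeding are matching factors too, yet both are in the LME. No reason is given for handling antibiotics and delivery mode differently.

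Two smaller matters belong to the same model. Siblings from multiple births share a mother, and matched infants share a set, but neither level is named. And a feeding variable with an unassigned range weakens both the matching and the diet covariate.

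**Working it through.** **Plan's own figures.** 720 to 1350 infants × 10% = 72 to 135 culture-proven cases; × 0.75 = 54 to 101 with complete stool sets, as stated. The minimum of 42 + 42 = 84 also reproduces (30% v 60%, two-sided 5%, power 80%, pooled variance). This point disputes none of these numbers.

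**Set-up.** The documents give no antibiotic prevalence, effect size, share of multiples or correlations, so the following are assumptions. The check simulates child-level means (equivalent to a child random intercept with balanced repeats), 54 cases, no true LOS effect, residual SD 1 and a two-sided 5% test. Controls are 1:1 unless stated.

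**Antibiotic term omitted.** Spurious LOS difference = antibiotic effect b × (exposure in cases − exposure in controls).

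| b (SD) | Cases v controls exposed, if unmatched | Expected bias | Type I error, unmatched | Type I error, exactly matched |
|---|---|---|---|---|
| 0.5 | 80% v 50% | 0.5 × 0.3 = 0.15 | 11.5% | 4.5% |
| 0.5 | 90% v 40% | 0.5 × 0.5 = 0.25 | 24.6% | 5.2% |
| 1.0 | 80% v 50% | 1.0 × 0.3 = 0.30 | 28.1% | 3.7% |
| 1.0 | 90% v 40% | 1.0 × 0.5 = 0.50 | 66.1% | 4.0% |

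With exact matching the simulated bias lay between −0.002 and 0.006 SD.

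**Partial matching.** Assume a residual difference of 20 points and two controls per case. Bias = 0.2 × 0.5 to 0.2 × 1.0 = 0.10 to 0.20 SD. With 54 cases, SE = √(1/54 + 1/108) = 0.167, so the shift is 0.6 to 1.2 SE and the type I error about 9% to 22%. With 101 cases, SE = √(1/101 + 1/202) = 0.122, the shift is 0.82 to 1.64 SE and the type I error about 13% to 37.5%.

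**Why exactness cannot be presumed.** The matching factor is prior antibiotic exposure for the infant. The article does not say whether that means any/none, type, duration or timing, and each infant gives up to four samples. Controls must be free of clinical and proven sepsis after 72 hours, so they cannot have been treated for an earlier late clinical episode; a case can.

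**Matched sets ignored.** With 10% to 30% of variance between sets, type I error is 2.1% to 3.7% for 1:1 and 1.8% to 3.9% for 1:2 matching. Standard errors are too large, so power is lost.

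**Multiples ignored.** With 10% to 30% of children in sibling pairs and within-pair correlation 0.3 to 0.6, the approximate design effect is 1 + 0.1 × 0.3 = 1.03 to 1 + 0.3 × 0.6 = 1.18. Type I error is 4.8% to 7.1% if siblings are in the same group and 3.0% to 5.4% if one is a case and the other a control.

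**Feeding categories.** More than 80% human milk means less than 20% formula. The next group starts above 50% formula. A formula share from 20% to 50% (human milk 50% to 80%) has no category. This follows from the printed limits without any assumption.

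**The case against.** The strongest answer is the matching. Both omitted factors are matching factors, and post-diagnosis samples are excluded. Under exact matching the bias is nil, and the figures of 0.15 to 0.50 SD describe unmatched controls, which the design does not intend. That stands, and it limits the point to residual confounding.

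Four stronger readings are tempting, and the documents do not support them:

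- A reader might infer that LOS effects necessarily absorb antibiotic effects. They can do so only where matching is coarse or the LME includes unmatched infants; the article settles neither.
- A reader might take the sentence on the strong impact of antibiotics as an admission about exposure before LOS. It concerns treatment after diagnosis, which the exclusion handles.
- A reader might infer that the planned larger number of controls breaks the matching. Several matched controls per case fit the wording equally well.
- A reader might infer that missing cluster levels give falsely narrow intervals throughout. For matched sets the error runs the other way; for multiples it depends on whether siblings share case status.

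It can also be said that an article condenses, and that a fuller plan may hold the complete model. This tempers the point but does not remove it: the article prints a definite factor list and cluster unit, and the list includes two matching factors while leaving out others. Finally, a mother-level intercept rests only on sibling sets, which may be few, so species-level fits could be unstable. That is a fair limit on the remedy.

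**Conclusion.** The point holds as a cheap improvement to the primary microbiome analysis. As printed, the LME leaves control of pre-LOS antibiotics and delivery mode entirely to matching of unstated precision and does not say that it runs on the matched sets. The possible bias in the LOS effect runs from about zero (exact matching), through 0.10 to 0.20 SD (an assumed residual difference of 20 points), to 0.15 to 0.50 SD (no matching on antibiotics). All of these rest on assumed exposure rates and an antibiotic effect of 0.5 to 1.0 SD. Missing set and sibling terms are secondary: the first costs power, and the second moves the type I error only to about 3% to 7%. The feeding gap is certain from the text, but how many infants it affects is unknown.

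A reader might extend the point to the Cox models or to a missing sex term in the LME. No fault is shown in either, so no change is asked for.

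**What to change.** - State that the LME is fitted on the matched sets.
- Add antibiotic exposure before each sample as a time-varying fixed effect, and mode of delivery as a fixed effect.
- Add a matched-set term besides the child intercept.
- For multiples, add a mother-level term where it can be estimated; otherwise report a sensitivity analysis keeping one infant per mother.
- Add a mixed-feeding category for 20% to 50% formula, so that the categories are exhaustive for both matching and the diet covariate.

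Antibiotic use and type, delivery type and multiple births are already captured, so the model changes cost a few parameters per species. Feeding records already entered need recoding, which is possible only where feed counts were kept; the article describes categories only, so this should be checked first.

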In resource-limited clinical settings, identification of pathogens causing neonatal sepsis and analysing AMR profiles remain challenging. Isolated bacteria are increasingly resistant to first and second-line antibiotics recommended by the WHO [12,13]. Extended-spectrum beta-lactamases (ESBL)-positive *Klebsiella* and *E. coli* spp. are reported to become the most common causes of neonatal sepsis in SSA with rapid emergence of carbapenem-resistant *Enterobacterales* [14]. New and affordable antibiotics for the treatment of multi-drug resistant (MDR) neonatal sepsis are lacking [15], therefore, in addition to the development of new drugs, infection prevention control (IPC) is pivotal.

Establishing reliable sepsis and AMR diagnostics through blood cultures of neonates admitted to NCUs is crucial for identifying bloodstream infections and determining antimicrobial susceptibility, allowing clinicians to prescribe antibiotics more efficiently and appropriately. A large multi-country study, including our study site, published by NEST360 in 2023, highlighted a significant gap: while 70% of neonates were prescribed antibiotics, only 6% had blood cultures taken, missing critical opportunities for infection detection [16]. The authors concluded that there is an urgent need to improve diagnostics, and develop individualized strategies for the prevention and treatment of LOS in LMICs.

The peak incidence of LOS occurs between the second and third week of life [17] after being exposed to various factors in the NCU environment and exposures to various invasive procedures and antibiotics altering the neonatal microbiome [18]. The hypothesis of gut dysbiosis preceding the development of LOS and NEC in preterm babies has been developed, based on findings of alterations in their gut microbiome in terms of specific metabolites and reduced biodiversity before disease onset [19–21]. Importantly, several conventional culture studies have demonstrated concordance between isolates cultured in blood and bacteria residing in the infants’ gut [22,23].

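### The stated microbiome mixed model does not carry the matching: no matched set, prior antibiotics, mode of delivery or sex. With exact matching this costs precision; otherwise the LOS coefficient is open to antibiotic confounding

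*Protocol article*

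**What the plan says.** **Design.** Under Study population and sample size, cases are compared with controls "matched for GA, sex, mode of delivery, type of feeding, and previous antibiotic exposure". The abstract also describes the sequencing comparison as one with matched controls. The same section later plans more controls than the minimum, without saying whether the additional ones are matched. Neither the matching ratio nor the type of matching (individual or frequency) is given.

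**Model.** The Statistical analysis section describes the "Association of relative abundances of microbial species with the factors of gestational age, days of life, diet, and LOS", using square-root-transformed abundances in linear mixed models with the child as the cluster. No other covariate and no other cluster level is named. The multivariable adjustment in that section belongs to the Cox models.

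**Antibiotics.** The same section states: "Antibiotic interventions following a LOS diagnosis are likely to have a strong impact on the microbiome composition". Its remedy is to exclude samples taken after the LOS diagnosis. Table 1 lists "Antibiotic exposure and type" and type of delivery among the candidate variables for predicting LOS and gut dysbiosis.

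**The concern.** Five factors define the matching. Two of them, gestational age and feeding, reappear in the model. Prior antibiotics, mode of delivery and sex do not, nor does the matched set. The analysis as stated therefore does not fit the design as stated.

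Two things are at stake. First, if matched infants resemble each other, a model that treats them as independent gives the wrong standard error for LOS and discards the precision that matching was meant to buy. Second, early antibiotics are the obvious rival explanation for a microbial pattern that precedes LOS. If exposure before the stool differs between cases and controls, the named model cannot separate the two. This bears on the primary research question, whether dysbiosis precedes LOS.

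**Working it through.** **1. The plan's own figure.** The inputs are "Assuming an alpha level of 5% and a power of 80" percent, and "we then expect gut dysbiosis in 30% of the neonates without and 60% of the children with LOS". With pooled variance (mean proportion 0.45):

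n = [1.96 × √(2 × 0.45 × 0.55) + 0.842 × √(0.30 × 0.70 + 0.60 × 0.40)]² / 0.30² = (1.379 + 0.565)² / 0.09 ≈ 42 per group.

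This reproduces "a minimal study number of 84 children (42 with and 42 without LOS) is needed". With unpooled variance the result is 39.2, so 40. Either way the calculation is for two independent groups. With the expected 54 to 101 complete case sets and as many controls, the power of that comparison is 89% to 99%. The powered comparison is thus one of dysbiosis proportions; the species-level mixed model is a separate analysis.

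**2. Exact matching, set ignored.** Let ρ be the within-set correlation (assumed 0.1 to 0.3; the documents give none). The true SE of the LOS contrast is √(1 − ρ) times the SE from a model without sets. Hence:

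- SE overstatement = 1/√(1 − ρ)
- type I error = 2 × [1 − Φ(1.96/√(1 − ρ))]
- power, where a set-based analysis has 80% = Φ(2.80 − 1.96/√(1 − ρ))

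| ρ | SE ratio | Type I error | Power |
|---|---|---|---|
| 0.1 | 1.05 | 3.9% | 77% |
| 0.2 | 1.12 | 2.8% | 73% |
| 0.3 | 1.20 | 1.9% | 68% |

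The error is conservative throughout.

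**3. Is the LOS coefficient biased?** Abundance is the response and LOS the regressor. Omitting antibiotics biases the LOS coefficient only if antibiotics differ between cases and controls:

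bias = antibiotic effect × difference in exposure proportion.

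Assume an effect of −0.8 SD, with exposure 80% in cases and 50% in unmatched controls (none of these is in the documents).

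- All sets matched on antibiotics: difference 0, bias 0.
- 70% of sets matched: 0.3 × (−0.8) × (0.80 − 0.50) = −0.07 SD.
- Unmatched controls: −0.8 × 0.30 = −0.24 SD.

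A simulation of one value per child (4000 runs, 1:1, no true LOS effect, antibiotics and set omitted) agrees:

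| Cases | Matching | Extra within-set correlation | Bias (SD) | Model SE | True SE | Type I error |
|---|---|---|---|---|---|---|
| 54 | exact | 0 | about 0 | 0.202 | 0.193 | 3.9% |
| 54 | exact | 0.2 | about 0 | 0.202 | 0.172 | 2.4% |
| 54 | exact | 0.4 | about 0 | 0.202 | 0.150 | 0.9% |
| 54 | 70% of sets | 0.2 | −0.07 | 0.203 | 0.179 | 3.6% |
| 54 | none | – | −0.24 | 0.204 | 0.202 | 22% |
| 101 | exact | 0.2 | about 0 | 0.148 | 0.128 | 2.4% |
| 101 | 70% of sets | 0.2 | −0.08 | 0.148 | 0.130 | 5.4% |
| 101 | none | – | −0.24 | 0.149 | 0.149 | 35% |

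The correlation column excludes the similarity that comes from shared antibiotic status. That is why the first row is already below 5%.

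In the 70% rows, a within-set analysis that still omits antibiotics rejects in 7.3% (54 cases) and 9.0% (101 cases). A set term alone is therefore not a full remedy; the antibiotic term has to go in with it.

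**4. Balance per infant is not balance per stool.** The simulation gives each child one yes/no exposure. The text leaves room for differences within that label:

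- Under C-reactive Protein, treatment for suspected early sepsis may be continued, changed or stopped, so its duration varies among exposed infants.
- Controls must be free of clinical and proven sepsis after 72 hours. A case may have had an earlier treated clinical episode.
- Treatment is not delayed for culture, and bottles are monitored for up to five days. If the diagnosis is dated by the culture result, some stools taken on treatment stay in the case data.

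As an illustration, assume 70% exposed and 0.1 SD per antibiotic day. One to two extra days in exposed cases then give 0.7 × 0.1 × (1 to 2) = 0.07 to 0.14 SD of bias, even with exact ever/never matching.

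**The case against.** - **Matching already handles antibiotics.** A reader might infer from the omitted term that the LOS coefficient is confounded by antibiotics. The documents do not support that: antibiotics are a matching factor, and complete matching gives a bias of about zero. This objection stands. What remains is conditional on loose matching, unmatched additional controls, or differences in exposure at each stool. The text neither states nor excludes any of these.
- **A condensed article need not list every term.** The sentence with the factor list also sets a prevalence filter for species, and a full analysis plan may add terms. This limits the point but does not remove it. The article names a specific covariate list and a specific cluster level, and these differ from its matching list.
- **There may be no sets.** Under frequency matching a set intercept has nothing to index. This is right, and the fix below is conditional on it.
- **The SE error is conservative and may be small.** This is also right. Gestational age and diet are in the model and would absorb part of the within-set similarity, so the lower end of the range may be nearer. The loss is in power, not in false markers.
- **Coarse matching is assumed.** The report that "while 70% of neonates were prescribed antibiotics, only 6% had blood cultures taken" suggests that a yes/no match would give most infants the same label. But it comes from a multi-country study of neonates that includes this site, not from this preterm population, and the matching level for antibiotics is not defined.

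**Conclusion.** The named mixed model does not reflect the matched design: three of the five matching factors and any matched set are missing, and pre-LOS antibiotics are not addressed in the model. With exact matching the consequence is lost precision, namely type I error of about 4% to 2% and power of about 77% to 68% instead of 80%, for an assumed within-set correlation of 0.1 to 0.3. Without exact matching, or with unequal antibiotic duration or recency at each stool, the LOS coefficient is open to confounding. The bias figures above (0.07 to 0.24 SD) and the 22% to 35% rejection rates only illustrate assumed inputs; they do not show that such a bias exists. The sample size and the powered comparison of dysbiosis proportions are not called into question by this point.

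**What to change.** In Statistical analysis, revise the paragraph on the mixed models as follows:

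- State that the case-control model uses the matched controls only. If unmatched controls enter, adjust for all five matching factors.
- State whether matching is individual or by frequency, and how prior antibiotic exposure is matched.
- Add as fixed effects antibiotic exposure up to each stool (as recorded in the eCRF), mode of delivery and sex.
- If matching is individual, add a random intercept for the matched set above the child.

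Place of birth, or a fixed look-back window such as seven days for recent antibiotics, is optional; neither is part of the stated matching.

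The cost is a few degrees of freedom and some wording, with no further recruitment or samples. One check is needed first: the article says that previous use and type of antibiotics are recorded, but not that dates or durations are. If dates are not captured, exposure up to each stool can only be entered as coarsely as the forms allow, and that should be stated as a limitation.

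### Siblings from multiple births can be enrolled, but the mixed model clusters on the child only and the Cox models state no allowance for siblings, so intervals for factors that siblings share would be somewhat too narrow

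*Protocol article*

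**What the plan says.** **Enrolment.** Under Study population and sample size, "All eligible preterm neonates admitted to the neonatal unit during the 18-month study period will be recruited". The exclusions that follow ("We will exclude infants whose mothers are below 18 years of age, have severe, life-threatening illness at the time of admission", then comorbidity, malformation and probiotic use) do not mention multiples and do not restrict enrolment to one infant per mother. Table 1 lists "Multiple births" among the neonatal candidate variables, so the authors expect siblings in the cohort.

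**Shared covariates.** The socio-economic column of Table 1 (for example "Self-rated household income") and nearly all of the maternal column (for example "Maternal antibiotic exposure 3 months before delivery") take one value per mother. So does gestational age when it is dated from the mother's records, as Demographic and clinical parameters describes.

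**Models.** Statistical analysis relates species abundance to gestational age, days of life, diet and LOS in a linear mixed-effects model, "where repeatedly collected microbiome data from each child is considered to cluster". For clinical endpoints, "Cox-proportional hazard regression will be utilized to investigate the relationship between the risk factors and risk to develop primary and secondary endpoints", with a hazard ratio and 95% confidence interval for each factor. The lme4 and survival packages are named. The article mentions no mother or pregnancy level, no frailty and no robust variance.

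**The concern.** A random intercept for the child absorbs the correlation between repeated stools from one infant. It does nothing for the correlation between two infants of one mother. If siblings' outcomes are positively correlated, two co-twins carry less information about a factor they share than two unrelated infants do. The model nevertheless counts them as two independent observations. Entering multiple birth as a covariate shifts the mean for multiples but does not model how alike two siblings are.

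What is at stake is the precision claimed for shared factors. In the mixed model this is gestational age, one of the four named terms, and it is tested species by species. In the Cox models it is the maternal and socio-economic factors; maternal risk factors are part of the first secondary research question.

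**Working it through.** **The plan's own figure.** The article gives no number for sibling dependence. Its one related calculation is 42 per group for dysbiosis of 30% against 60% (5% two-sided, 80% power). The pooled two-proportion formula reproduces it: [1.960 × √(2 × 0.45 × 0.55) + 0.842 × √(0.21 + 0.24)]² / 0.30² ≈ 42.0, with power 80.0%. It treats infants as independent, but it concerns cases against controls rather than a factor shared by siblings, and is not challenged here.

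**Inputs that the article does not give (assumptions).**
- f, the share of infants with an enrolled co-twin: 0.20 to 0.40.
- ρ, the within-pair correlation of the infant-level outcome: 0.2 to 0.6.

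**Step 1, whole cohort, factor constant within a pair.** The design effect is DE = 1 + f × ρ. True variance is DE times the variance reported under independence, so variance is understated by 1 − 1/DE and the standard error by 1 − 1/√DE. The true size of a nominal 5% test is 2 × [1 − Φ(1.96/√DE)].

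| f | ρ | DE | √DE | Variance understated | SE understated | True size |
|---|---|---|---|---|---|---|
| 0.20 | 0.2 | 1.04 | 1.020 | 3.8% | 1.9% | 5.5% |
| 0.40 | 0.6 | 1.24 | 1.114 | 19.4% | 10.2% | 7.8% |

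A milder assumption, f = 0.1 and ρ = 0.1, gives DE = 1.01, √DE = 1.005 and size 5.1%. A harsher one, f = 0.4 and ρ = 0.8, gives DE = 1.32, √DE = 1.149 and size 8.8%.

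**Step 2, simulation check.** Infant means were simulated with N = 400 and 4,000 runs per setting. This matches a child random intercept with equal numbers of samples per child. The Monte Carlo standard error at 5% is √(0.05 × 0.95/4000) ≈ 0.3 percentage points.

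| f | ρ | Size, mother-level factor | Size, factor independent between siblings |
|---|---|---|---|
| 0.2 | 0.3 | 6.2% | 4.9% |
| 0.2 | 0.5 | 6.8% | 5.2% |
| 0.2 | 0.8 | 7.5% | 4.6% |
| 0.4 | 0.3 | 6.8% | 5.2% |
| 0.4 | 0.5 | 7.1% | 4.5% |
| 0.4 | 0.8 | 8.7% | 4.4% |

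The inflation appears for shared factors only.

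**Step 3, nested microbiome subset.** The abstract and Study design describe sequencing in cases and matched controls, so a pair matters only if both siblings are analysed. Take 101 complete cases out of 1,350 recruited, and assume 1 to 4 controls per case. The analysed share is then 202/1350 = 15% to 505/1350 = 37%. The low end of the article's range, 54 cases out of 720, gives the same shares. If siblings are selected independently, the effective f is 0.20 × 0.15 = 0.03 to 0.40 × 0.374 = 0.15. With ρ of 0.2 to 0.6:
- DE = 1 + 0.03 × 0.2 = 1.006 to 1 + 0.15 × 0.6 = 1.09.
- √DE = 1.003 to 1.044.
- True size = 5.1% to 6.0%.

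**Step 4, LOS as outcome.** A 500-replicate simulation at n = 720 and 1,350, with LOS incidence of 9–19%, gave a size of at most about 6% when siblings were ignored. It used logistic rather than Cox regression. Its Monte Carlo standard error is √(0.05 × 0.95/500) ≈ 1 percentage point, so it shows only that the effect is small.

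**The case against.** - **The Cox part rests on silence.** The article names the model, the intervals and the package, but no variance estimator. An analysis plan that is not shown could cluster on mother. This stands, and the Cox part is therefore the weaker half. The mixed-model part is different, because there the article names the clustering unit and it is the child.
- **The explicit part touches few shared factors.** Of the four named terms, only gestational age is necessarily common to siblings. This stands and sets the scope of the point.
- **The subset dilutes the effect.** This also stands and gives the lower range in Step 3. Matching on gestational age and mode of delivery, or LOS that clusters in sibships, could make siblings enter together more often than by chance. The 5.1–6.0% depends on that not happening.
- **The sizes are assumed.** They are: neither f nor ρ can be recovered from the article.

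Two stronger readings are tempting. A reader might infer that the primary contrast of dysbiosis before LOS is compromised. The article does not support this: LOS can differ between siblings, and the check found 4.4–5.2% for a factor varying independently between them. A reader might also infer from the phrase "in relation to the microbiome of the mother" that one mother's stool is counted two or three times in a mother–infant comparison. The article states no model, test or unit for that comparison, so no double counting can be claimed.

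**Conclusion.** The point holds as a minor refinement. Followed as written, the mixed model treats co-multiples as independent, and its intervals for gestational age would be somewhat too narrow. The same applies to maternal and socio-economic hazard ratios if the Cox models are run without a sibling term.

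With 20–40% of infants in twin pairs and a correlation of 0.2–0.6, variance is understated by about 4–19%, and a nominal 5% test runs at about 5.5–7.8%. The more relevant range for the sequenced subset is about 5.1–6.0%, given independent selection of siblings and 1–4 controls per case. For LOS as outcome the effect is small. The direction requires only a positive correlation between siblings; the size rests wholly on the assumed values.

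**What to change.** - **Mixed models (lme4):** add a random intercept for mother, with child nested in mother.
- **Cox models (survival):** use a robust variance clustered on mother.
- **Matching:** state whether a sibling may serve as the matched control of a case.

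This is one term per model in the packages already named. Mothers and infants are enrolled together, so no new data should be needed, and the change can be made before analysis.

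The cost is small but not nil. The mother variance is separated from the child variance only by sibling sets. If few are sequenced, it may be poorly estimated or fall on the boundary at zero in some species models. In that case, keep the child intercept and report a sensitivity analysis with one infant per mother, accepting that it discards some infant data.
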